## Abstract

**Background:**

Culturally responsive nursing involves delivering care that respects and reflects patients’ cultural values, communication patterns, and belief systems. In the Indian context, increasing rural-to-urban migration along with the expansion of medical tourism, estimated to have attracted 2.1 million international patients in 2024, has intensified the need for culturally competent nursing care. Although educational interventions in this area have shown encouraging results, there remains a lack of well-designed randomized controlled trials (RCTs) in India. For the purpose of this study, structured training is understood as a planned, session-based approach to learning that includes activities such as simulation exercises, case-based discussions, and guided reflection.

**Objective:**

This study aims to develop, validate, and evaluate a culturally competent care module (CCCM) through a 3-phase RCT, assessing its effects on nurses’ cultural competence and patient satisfaction.

**Methods:**

This 3-phase parallel-group RCT is being conducted in the medical-surgical wards of the Acharya Vinoba Bhave Rural Hospital, Wardha, Maharashtra, India (2024-2026). In phase 1 (completed), the CCCM was developed via thematic analysis of 20 interviews with nurses, educators, and patients. In phase 2 (completed), the CCCM and a patient satisfaction tool were validated using a 2-round Delphi process involving 15 experts (CCCM: content validity index ≥0.89; patient satisfaction tool: Cronbach α=0.87-0.92). Phase 3 is ongoing: 55 nurses are randomized in a 1:1 ratio to either the CCCM (5×1-hour sessions+boosters) or routine care. The primary outcome is the postintervention Cultural Competence Assessment Tool for Nurses score, while secondary outcomes include subscales, patient satisfaction, and 90-day retention. The sample size is calculated using G*Power based on an anticipated effect size of 0.82. Participants are randomly allocated through computer-generated block randomization stratified by seniority, and outcome assessors and data analysts are blinded to group allocation. Data will be analyzed using SPSS (intention-to-treat, linear mixed-effects models; *P*<.05). Patient satisfaction outcomes will be evaluated using data from 120 patients.

**Results:**

Phases 1 and 2 were completed in July 2025. In phase 3, 110 (100%) nurses were successfully enrolled and randomized, with 55 participants assigned to each group. The intervention was delivered as planned, and postintervention data collection reached 70% completion. Additionally, of the planned 120 patients, 92 (77%) were enrolled for the patient satisfaction assessment. Full data analysis is expected to be completed by June 2026.

**Conclusions:**

This trial will provide evidence on the CCCM’s noninferiority or superiority to routine care for enhancing cultural competence and satisfaction, supporting scalable training amid India’s demographic shifts.

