The conceptual foundation of the CCCM draws on established theoretical frameworks, including Campinha-Bacote’s [2] model, Giger and Davidhizar’s [12] transcultural assessment model, and Purnell’s [13] model for cultural competence. In addition, organizational perspectives emphasize the role of cultural alignment in enhancing health care delivery and patient outcomes [14]. International policy guidance, such as the World Health Organization’s framework on intercultural health care, further supports the integration of cultural competence training to address health inequities [15].

Systematic reviews indicate that structured cultural competence training improves communication outcomes and patient satisfaction when compared with routine care [16]. However, rigorously designed randomized controlled trials (RCTs) in India that assess both nurse-level and patient-level outcomes remain limited.

This study therefore aims to develop, validate, and evaluate the CCCM using a RCT design. It is hypothesized that nurses who receive CCCM training will demonstrate improved cultural competence (Cultural Competence Assessment Tool for Nurses [CCAT-N] scores; Multimedia Appendix 1) and that their patients will report greater satisfaction compared to those receiving standard care.

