### Sample Size Determination

The sample size is calculated based on the primary outcome of cultural competence measured using the CCAT-N. Pilot data indicated a large effect size (Cohen *d*≈0.8). Assuming a 2-tailed significance level of .05 and a statistical power of 90%, a minimum of 34 participants per group is required. After accounting for a potential attrition rate of 20%, the final sample size is set at 55 participants per group, resulting in a total of 110 nurses.

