### Randomization and Blinding

Participants are randomly assigned in a 1:1 ratio to the intervention or control group using a block randomization approach with stratification by ward seniority (junior vs senior nurses). Allocation concealment is ensured using sequentially numbered, opaque, sealed envelopes prepared independently before enrollment. Blinding of participants is not feasible due to the nature of the educational intervention. However, outcome assessors and data analysts remain blinded to group allocation. To reduce contamination, training sessions are conducted during off-duty hours, intervention materials are restricted to the intervention group, and patient allocation is organized after completion of training. The control group is offered access to the CCCM after study completion.

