### Study Phases

#### Phase 1

The CCCM was developed using a qualitative exploratory design. In-depth interviews were conducted with registered nurses, nurse educators, sociologists, psychologists, and patients from diverse cultural backgrounds (Multimedia Appendix 2). The interviews explored communication barriers, culturally sensitive practices, and sociocultural considerations in care delivery. Data were analyzed using Braun and Clarke’s [17] 6-step thematic analysis framework. Emergent themes informed the structure, learning objectives, and content domains of the CCCM.

#### Phase 2

Validation of the CCCM and patient satisfaction tool: the CCCM and a culturally sensitive patient satisfaction tool were validated using a 2-round Delphi process involving experts in transcultural nursing and health care communication. Content validity was assessed in terms of relevance, clarity, and applicability. The CCCM achieved a content validity index (CVI) of ≥0.89. Revisions were incorporated based on expert feedback.

Phases 1 and 2 of the study are completed. Phase 3 is planned as per the following details.

#### Phase 3

RCT: participants are randomized to either the intervention group (CCCM plus routine care) or the control group (routine care only). The effectiveness of the intervention is assessed through comparison of outcomes between groups.

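### The abstract's conclusion offers noninferiority as a possible finding, but the article describes only a two-sided superiority trial of an add-on module and gives no margin

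*Protocol article*

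**What the plan says.** The Conclusions paragraph of the abstract says the trial will provide evidence on the module's "noninferiority or superiority to routine care for enhancing cultural competence and satisfaction", and goes straight on to say that this supports scalable training. Noninferiority is not mentioned anywhere else in the article.

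The other sections describe superiority:

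- **Introduction:** "It is hypothesized that nurses who receive CCCM training will demonstrate improved cultural competence". The same sentence expects greater satisfaction among these nurses' patients.
- **Sample Size Determination:** "Pilot data indicated a large effect size" (Cohen d about 0.8), and then "a statistical power of 90%, a minimum of 34 participants per group is required". The test is two-tailed at .05. The abstract's Methods give the effect size as 0.82.
- **Study Phases, Phase 3:** nurses are randomized to "the intervention group (CCCM plus routine care) or the control group (routine care only").
- **Data Analysis:** postintervention scores are compared by a two-tailed t test, or by analysis of covariance where baselines differ, with two-tailed P<.05 as the criterion. The abstract and Planned Data Analysis name a linear mixed-effects model instead. All of these are tests of a difference.
- **Anticipated Findings:** moderate-to-large improvements are expected.

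**The concern.** A noninferiority conclusion needs a margin, a rule for comparing a confidence limit with that margin, and a comparator for which being no worse is a useful result. The article supplies none of the three. Without a margin there is no criterion by which the trial could succeed or fail on noninferiority, so the abstract claims something the described design cannot deliver.

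The practical risk is in interpretation. The abstract ties both possible conclusions to scalable training, so a non-significant difference could be presented as noninferiority and then as a reason to roll the module out. The Limitations section concedes that informal knowledge sharing between arms cannot be ruled out. Such sharing pulls the arms together, which makes a loose noninferiority claim easier to reach.

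The add-on comparison makes the phrase less useful still. The intervention arm receives everything the control arm receives, plus five one-hour sessions and three boosters. Showing that this is no worse than routine care alone gives no reason to take on the extra work.

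**Working it through.** **1. Which hypothesis was the trial sized for?**

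Inputs from Sample Size Determination: d = 0.8, two-sided alpha 0.05, power 90%. Allocation is 1:1 (Randomization and Blinding). The article gives no raw SD, so everything here is in SD units.

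Formula (normal approximation): n per group = 2(z₁₋α/₂ + z₁₋β)² / d².

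- Two-sided, d = 0.8: 2(1.960 + 1.282)² / 0.64 = 21.01 / 0.64 = 32.8, so 33. The exact noncentral t calculation gives **34**, the stated figure.
- Two-sided, d = 0.82: 32 (normal), 33 (noncentral t).
- One-sided 0.05, d = 0.8: 27 and 28. With d = 0.82: 26 and 27. Neither reproduces 34.

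The stated 34 is therefore a two-sided superiority calculation.

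**2. What could the trial say about noninferiority?**

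The article gives no margin, so those below are assumptions. Take a true difference of 0, one-sided alpha 0.025 and margin M in SD units.

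Power = Φ(M√(n/2) − 1.960). Required n per group for 90% power = 2(1.960 + 1.282)² / M². The columns use 55 per group (the stated target) and 44 per group (55 × 0.8, the stated 20% attrition).

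| Assumed M (SD) | n per group for 90% power | Power, 55 per group | Power, 44 per group |
|---|---|---|---|
| 0.2 | 526 | 18% | 15% |
| 0.3 | 234 | 35% | 29% |
| 0.5 | 85 | 75% | 65% |
| 0.7 | 43 | 96% | 91% |

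Example: M = 0.3, n = 55 gives 0.3 × √27.5 − 1.960 = 1.573 − 1.960 = −0.387, and Φ(−0.387) = 0.35.

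Only a very wide margin, close to the planned benefit itself, would be adequately powered.

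**3. Does P>.05 carry information on noninferiority?**

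The half-width of the 95% interval is t₀.₉₇₅ × √(2/n): about 0.38 SD with 55 per group and 0.42 SD with 44. With 55 per group, a non-significant estimate lies between −0.38 and +0.38. Its lower confidence limit can then be anywhere from about −0.76 to 0. A non-significant result alone therefore does not show that the module arm is not worse by any particular amount.

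**4. Could a margin be added now?**

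Phase 3: RCT Implementation Status reports all 110 nurses randomized and immediate postintervention assessments conducted in November 2025. The abstract's Results put postintervention collection at 70% complete. On either account, outcome data were collected before any margin appeared in the article.

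**The case against.** The strongest reply is that this is one phrase in an abstract. The sections that govern the trial agree on superiority, and no sample size or analysis depends on the phrase. The body also makes its claims conditional: Anticipated Findings and the closing Conclusions speak of what follows if the trial succeeds or the module proves effective. All of that stands and limits the weight of the point. It does not remove it, because the abstract sentence carries no such condition and names a conclusion the design does not support.

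A margin might exist in a full protocol or analysis plan that is not shown, so the claim here is only that none appears in the article. The article does, however, state its hypothesis, sample size and significance rule, and these do not fit the abstract's claim.

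A reader might infer several stronger things:

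- **That a large share of trials like this would end in a false noninferiority claim.** At an assumed true d of 0.5 with 44 per arm, the t test misses in about 36% of trials. That is the type II error of the superiority test, and at the planned d of 0.8 it is about 4%. At d = 0.5 the module really is better, so calling it no worse would not be false.
- **That patients cared for by nurses of both arms add further dilution.** The article says patient allocation is organized after training but not how patients are linked to nurses, so mixed-arm care is not established.
- **That every non-significant result is inconclusive.** With 55 per arm and a half-width of 0.38 SD, a non-significant estimate has an upper limit below about 0.76, which excludes the planned 0.8. That would be informative evidence against the planned effect.

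**Conclusion.** The point holds as an error of wording with consequences for interpretation. The abstract names noninferiority as a possible conclusion, while the hypothesis, sample size, comparison and analysis rule support only superiority of the module plus routine care over routine care alone.

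The effect on the trial's figures is nil: 34 per group reproduces and nothing is recalculated. What changes is what the trial may claim if the difference is not significant. The noninferiority power figures rest on assumed margins and a true difference of zero, and only show that the sample would not support such a claim at small or moderate margins. That a null result would be misread is a risk created by the wording. The article does not announce any such intention, and the point does not put the superiority comparison itself in doubt.

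**What to change.** In the abstract's Conclusions, delete the reference to noninferiority and state that the trial tests superiority of the module plus routine care over routine care alone. Make the sentence on scalable training conditional on that superiority being shown, as the body of the article already does.

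State that the between-group difference will be reported with its 95% confidence interval whatever the P value, and that a non-significant result will not be presented as noninferiority or as support for scale-up. The interval can then be read for what it excludes, including the planned effect. Do not add a noninferiority margin at this stage.

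The cost is a sentence or two. No sample size, test or data collection changes. It should be done before the final analysis, expected by June 2026.

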**Trial Registration:**

Clinical Trials Registry–India (CTRI) CTRI/2025/06/088982; https://ctri.nic.in/Clinicaltrials/pmaindet2.php?EncHid=MTMzMjQ5&Enc=&userName=

**International Registered Report Identifier (IRRID):**

DERR1-10.2196/84015

## Introduction

Culturally responsive nursing practice extends beyond routine clinical competence and requires the ability to deliver care that is consistent with patients’ cultural values, communication patterns, spiritual beliefs, and health practices [1]. In nursing literature, cultural competence is not viewed as a fixed end point but as a continuous and evolving process. Campinha-Bacote’s [2] process model conceptualizes this progression through 5 interrelated constructs: cultural awareness, cultural knowledge, cultural skill, cultural encounters, and cultural desire. The model highlights the importance of reflective practice, experiential learning, and ongoing engagement with culturally diverse populations.

The growing need for cultural competence in India is closely linked to ongoing demographic transitions. Rapid rural-to-urban migration has diversified patient populations in metropolitan and semiurban health care settings [3]. At the same time, India has become a prominent destination for medical value travel, with approximately 2.1 million international patients reported in 2024 [4]. This trend reflects broader global patterns, with more than 300 million international migrants documented worldwide by mid-2024 [5]. These changes have made culturally responsive care an essential component of quality health care delivery.

Evidence from international settings demonstrates the effectiveness of structured cultural competence training. In this context, structured training refers to formally designed, curriculum-based educational interventions that include clearly defined learning objectives; standardized content; and guided learning strategies such as simulation exercises, case-based discussions, role-play, and reflective practice sessions. For example, simulation-based intercultural scenarios used in the United States and case-based training modules integrated into continuing education programs in Europe have demonstrated improvements in communication skills and culturally appropriate clinical decision-making. A recent randomized trial (2025) further reported significant improvements in cultural knowledge and sensitivity following structured educational intervention [2]. A multicenter Ethiopian study also identified a positive association between nurses’ cultural competence and equitable health care delivery [6], while a contemporary scoping review concluded that structured educational modules strengthen communication and responsiveness to patients’ needs [7].

Within the Indian context, available evidence suggests progress but also notable limitations. Quasi-experimental studies have reported improvements in nurse-patient communication following targeted training interventions [8]. However, challenges such as linguistic diversity and religious plurality continue to influence care delivery [9]. Findings from medical tourism settings indicate that perceived cultural insensitivity can negatively affect patients’ trust and satisfaction [10]. Despite these insights, a key limitation in Indian research is the lack of rigorously designed, context-specific interventions evaluated through robust methodologies. Most studies rely on quasi-experimental designs and do not assess long-term retention of skills. Research from rural Maharashtra further highlights a disconnect between awareness and actual practice of cultural competence [11].

In response to these gaps, this study proposes the development and evaluation of a culturally competent care module (CCCM) tailored for practicing nurses. The module is designed as a structured educational intervention aimed at improving both cultural competence and patient-centered care outcomes.

The conceptual foundation of the CCCM draws on established theoretical frameworks, including Campinha-Bacote’s [2] model, Giger and Davidhizar’s [12] transcultural assessment model, and Purnell’s [13] model for cultural competence. In addition, organizational perspectives emphasize the role of cultural alignment in enhancing health care delivery and patient outcomes [14]. International policy guidance, such as the World Health Organization’s framework on intercultural health care, further supports the integration of cultural competence training to address health inequities [15].

Systematic reviews indicate that structured cultural competence training improves communication outcomes and patient satisfaction when compared with routine care [16]. However, rigorously designed randomized controlled trials (RCTs) in India that assess both nurse-level and patient-level outcomes remain limited.

This study therefore aims to develop, validate, and evaluate the CCCM using a RCT design. It is hypothesized that nurses who receive CCCM training will demonstrate improved cultural competence (Cultural Competence Assessment Tool for Nurses [CCAT-N] scores; Multimedia Appendix 1) and that their patients will report greater satisfaction compared to those receiving standard care.

## Methods

### Study Design

This study is a 3-phase, parallel-group RCT with individual-level allocation. It is being conducted between 2025 and 2026 in the medical-surgical wards of the Acharya Vinoba Bhave Rural Hospital, Wardha, Maharashtra, India. Phases 1 and 2 focused on the development and validation of the CCCM and have been completed. This protocol describes phase 3, which evaluates the effectiveness of the CCCM through a randomized comparison.

### Study Setting

The trial is being conducted in 6 independent medical-surgical wards of the Acharya Vinoba Bhave Rural Hospital, a tertiary care teaching hospital serving a culturally and socioeconomically diverse population from rural and semiurban regions of Maharashtra. Each ward is staffed by 2 to 3 registered nurses per shift, which supports individual randomization while reducing the risk of contamination between study groups.

### Participants

A total of 110 registered nurses are being recruited. Eligible participants are nurses currently working in medical-surgical wards with at least 1 year of clinical experience. Written informed consent is obtained prior to participation. Nurses who have previously completed formal training in cultural competence are excluded to minimize bias related to prior exposure.

### Sample Size Determination

The sample size is calculated based on the primary outcome of cultural competence measured using the CCAT-N. Pilot data indicated a large effect size (Cohen *d*≈0.8). Assuming a 2-tailed significance level of .05 and a statistical power of 90%, a minimum of 34 participants per group is required. After accounting for a potential attrition rate of 20%, the final sample size is set at 55 participants per group, resulting in a total of 110 nurses.

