#### Phase 2: Validation of the CCCM and Study Instruments

Phase 2, conducted between June and July 2025, involved the validation of the CCCM and the culturally adapted patient satisfaction tool. Content validation was performed using a 2-round modified Delphi technique involving 15 experts, including sociologists (n=2), psychologist (n=1) physician (n=1), nurse educators (n=8), and clinical nursing leaders (n=3).

The CCCM achieved a CVI of 0.89, while the patient satisfaction tool demonstrated a CVI of 0.92, indicating high agreement among experts regarding relevance and clarity. The CCAT-N, adapted for this study, demonstrated strong psychometric properties. Internal consistency was high (Cronbach α=0.87), and test-retest reliability over a 14-day interval was satisfactory (*r*=0.82). The tool also showed good sensitivity to change, with a pilot study indicating a large effect size (Cohen *d*=0.82). The 15-item patient satisfaction tool, measured on a 5-point Likert scale, demonstrated high internal consistency (Cronbach α=0.89). Construct validity was established through exploratory factor analysis, which identified 2 primary factors accounting for 73% of the total variance, namely, “respect for cultural practices” (42%) and “effective communication” (31%).

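### The move from 34 to 55 nurses per group is not explained by 20% attrition, which gives 43, and the abstract's Methods paragraph reports 55 nurses where 110 are meant

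*Protocol article*

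**What the plan says.** The sample size is built in two steps in Methods, Sample Size Determination. The effect size comes first: "Pilot data indicated a large effect size (Cohen *d*≈0.8"). With a two-sided 5% significance level and 90% power, the section concludes that "a minimum of 34 participants per group is required". The second step is the allowance for loss: "After accounting for a potential attrition rate of 20%, the final sample size is set at 55 participants per group", for a total of 110.

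The total of 110 is repeated in the Participants section ("A total of 110 registered nurses are being recruited"), in the abstract's Results, and in the Phase 3 implementation status. The last two also give 55 per group. The abstract's Methods paragraph differs: "55 nurses are randomized in a 1:1 ratio". That paragraph also gives the planning effect to two decimals: "The sample size is calculated using G*Power based on an anticipated effect size of 0.82".

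The source of the effect appears in the Phase 2 validation results, among the psychometric properties of the CCAT-N: "The tool also showed good sensitivity to change, with a pilot study indicating a large effect size", with d = 0.82.

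**The concern.** A sample size statement should let a reader go from the inputs to the number enrolled. Here the last step fails. The text names 20% attrition as the only reason for moving from 34 to 55 per group, and 20% attrition does not produce 55. Twelve nurses per group (55 − 43), or 24 in all, have no stated basis.

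The abstract adds a second difficulty. Read literally, its Methods paragraph halves the trial. Readers and evidence synthesists often extract the sample size from the abstract.

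What is at stake is whether the published justification can be checked and whether the enrolled number is reported consistently. Enrolment is complete at 110, so the number of nurses is not in question.

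**Working it through.** **Inputs.** From Sample Size Determination: d ≈ 0.8, two-sided alpha 0.05, power 90%, 34 per group, attrition 20%, final 55 per group. From Randomization and Blinding: 1:1 allocation. From Data Analysis: an independent-samples t test on postintervention CCAT-N scores.

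**Step 1: the plan's own 34.** A two-sample t test using the noncentral t distribution needs 33.8 per group at d = 0.80, which rounds up to 34 (power 90.2%). At d = 0.82 it needs 32.2, so 33. The stated 34 reproduces.

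**Step 2: the attrition allowance.** The formula is n / (1 − attrition).

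- 34 / (1 − 0.20) = 34 / 0.80 = 42.5, so 43 per group and 86 in total.
- The cruder 34 × 1.20 = 40.8 gives 41 per group and 82 in total.

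Neither gives 55.

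**Step 3: what attrition would give 55?** 1 − 34/55 = 0.382, about 38%.

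**Step 4: could another convention explain 55 with 20% attrition?**

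| Variant at d = 0.8 | Per group before loss | After 20% allowance |
|---|---|---|
| 95% power instead of 90% | 41.6 | 52 |
| Worst-case efficiency loss for a rank test (0.864) | 39.1 | 49 |
| 20% allowance applied twice (34/0.64 = 53.1; not a standard step) | – | 54 |

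None reaches 55. Working backwards, 55 × 0.80 = 44, so 55 is the figure for a requirement of 44 completers per group. A planning effect of d = 0.70 at 90% power needs 43.9, so 44. That is a possible origin of 55, but the article mentions no such effect size, so it remains a conjecture.

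**Step 5: consequence for power.** With 55 per group and 20% loss, 44 per group are analysed. Power is 96.0% at d = 0.80 and 96.7% at d = 0.82. The effect detectable with 90% power is 0.70.

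**Step 6: the abstract.** The two figures for the number randomized, side by side:

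| Place | Nurses |
|---|---|
| Abstract, Methods | 55 randomized 1:1 |
| Abstract, Results | 110, 55 per group |
| Participants | 110 |
| Sample Size Determination | 110, 55 per group |
| Phase 3 implementation status | 110, 55 per group |

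Four of the five agree, so the abstract's Methods paragraph is the one in error.

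**The case against.** The best defence is that nothing harmful follows. The 34 is presented as a minimum and 55 as the number chosen, so the unexplained part is surplus and the error runs in the safe direction. The abstract's 55 is almost certainly a dropped *per group*, put right by the next paragraph of the same abstract. The difference between 0.82 and about 0.8 is rounding and moves the requirement by one nurse per group. All of this stands. It limits the weight of the point but does not remove it, because the text still presents 55 as the result of a calculation that gives 43.

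Three stronger readings are tempting, and the article supports none of them.

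- *The power calculation as a whole is wrong.* It is not. The 34 per group reproduces, and only the attrition step fails.
- *The trial has only 55 nurses and is underpowered.* With 27 or 28 per group, power at d = 0.8 would be 82–84% before loss and about 73–74% after 20% loss. Every other statement of the number, including the enrolment report, contradicts that reading.
- *The pilot effect is a within-nurse change, so the t test falls short of 90% power.* Sensitivity to change often refers to a pre-post effect, but the article does not describe the pilot's design, and a two-group pilot could also show responsiveness. A shortfall needs three assumptions: that 0.82 is a pre-post effect, that it is standardized by the SD of the change, and that the pre-post correlation r is high. Then between-group d = 0.82 × √(2(1 − r)). At r = 0.5, 0.7 and 0.82 this gives d = 0.82, 0.64 and 0.49, and with 44 per group the power is 97%, 84% and 63%. The last value of r is the 14-day test-retest figure, borrowed here for a correlation across a training programme. The range runs from no effect on power to a material one, and nothing in the article places the trial within it. Moreover, Planned Data Analysis names a linear mixed-effects model for the primary outcome, so the unadjusted t test is not the only analysis described. What remains is a question to the authors.

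**Conclusion.** The point holds in a limited form. On the stated inputs, 20% attrition takes 34 per group to 43 (86 in total), not to 55 (110 in total); the gap is 12 per group, and 55 would correspond to about 38% attrition. The abstract's Methods paragraph misstates the number randomized by a factor of two. Both conclusions rest only on figures in the article and need no outside assumption.

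The trial is larger than its stated inputs require. The 96% power with 44 completers per group assumes that 0.8 is a between-group effect on postintervention scores and that the analysis is the t test described. What the pilot effect measures is an ambiguity to resolve, not a demonstrated error.

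**What to change.** Change the wording only; enrolment stays as it is.

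1. In Sample Size Determination, if no other basis for 55 exists, restate along these lines: *34 per group are needed (d ≈ 0.8, two-sided .05, 90% power); a 20% attrition allowance gives 43 per group (86 in total). In all, 110 nurses were enrolled; with 20% attrition, the 44 completers per group give about 96% power at d = 0.8, or 90% power at d = 0.70.* If 55 was chosen for another reason, such as a smaller planning effect or a larger allowance for loss, give that reason instead. It should be the basis actually used at planning.
2. In the abstract's Methods paragraph, write 110 nurses, 55 per group.
3. As a clarification, state in the Phase 2 results or in Sample Size Determination whether the pilot d of 0.82 is a between-group or a pre-post effect and, if pre-post, how it was standardized.

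The cost is a few sentences, with no additional nurses or data.
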